## Abstract

**Background:**

The benefits of physical activity and cardiovascular rehabilitation on the reduction of cardiovascular risk are well documented. Despite this, significant barriers and challenges remain in optimizing patient risk factors post acute coronary syndromes (ACS) and ensuring patient compliance. Consumer wearable personal activity trackers represent a cost effective and readily available technology that may aid in this endeavour.

**Methods:**

UP-STEP ACS is a prospective single-blinded, two-arm, parallel, randomized control trial with an aim to enrol 200 patients all undertaking cardiac rehabilitation. It will assess the affect that personal activity monitors have on change in exercise capacity in patients post acute coronary syndromes primarily measured by a six-minute walk test (6MWT). Secondary end points will be the improvement in other cardiovascular risk factors, namely; blood lipid and glucose levels, weight, waist circumference, along with mood, quality of life and cardiac rehabilitation adherence. Patients will be randomized to either receive a personal activity tracker or standard post hospital care during their index event. After the 8- week intervention period, patients will return for a clinical review and repeat of baseline assessments including the 6MWT.

**Discussion:**

The utility and impact on exercise capacity of personal activity trackers in patient’s post-acute coronary syndrome has not been assessed. This study aims to add to the scientific evidence emerging regarding the clinical utility and validity of these devices in different patient population groups. If proven to be of benefit, these devices represent a cost effective, easily accessible technology that could aid in the reduction of cardiovascular events.

**Trial registration:**

The trial has been registered with the Australian New Zealand Clinical Trials Registry (ANZCTR). The registration number is ACTRN12617000312347 (28/02/2017).

## Background

The increased understanding of cardiovascular risk factors and the importance of aggressive primary and secondary prevention measures have aided significantly in the reduction of cardiovascular disease and events. However, despite the evidence, the application of these interventions is far from optimal [1–3]. Coronary heart disease (CHD) still represents the leading cause of mortality and morbidity in Australia with almost 20,000 deaths in 2013 attributed to CHD [4]. This is also reflected globally with the World Health Organisation (WHO) attributing 8.76 million deaths, or 15.5% of the estimated 56.4 million deaths in 2015 to CHD [5].

Numerous observational studies have shown that there is an increased risk of recurrent cardiac events in patients who are known to have CHD and in particular those who have survived an acute coronary syndromes (ACS), with new events occurring most commonly within the first year following the index event [6]. Australian data has estimated that 34% of all hospital admissions for ACS are repeat events with this representing a significant burden on the health care system economically, and a poor prognostic marker for patients individually [7].

Aggressive secondary prevention is vital in reducing the risk of recurrent events and forms the pillar of secondary risk reduction. From a pharmacological perspective, guidelines are readily accessible and routinely followed immediately post cardiac event, however there remains inherent challenges with compliance and follow-up. The recent TRANSLATE-ACS study [8] showed that 31% of myocardial infarction (MI) patients had stopped taking at least 1 medication by 6 months, with other studies showing dosage is often suboptimal post discharge with only 1 in 3 patients within the suggested dosage target and only 25% of patients prescribed a dosage increase after discharge [9]. Therefore, close patient follow-up, education and appropriate dose titration is vital.

Non-pharmacological secondary prevention is generally targeted at lifestyle modification, with the most common interventions focused around weight loss, smoking cessation, cardiovascular education programs, implementation of a healthy diet and regular physical activity and psychosocial support. Cardiac rehabilitation (CR), a comprehensive evidence based vehicle used to deliver much of the education, engagement and monitoring of lifestyle modifications have been shown to have a significant effect on both mortality and hospital readmission rates with reductions of 41 and 32% respectively [10]. A recent Cochrane review confirmed this, albeit to a lesser degree, showing a 13% decrease in all-cause mortality and a 26% decrease in cardiovascular mortality in those attending CR [11].

Despite its proven benefits, CR referral and participation rates still remain low. In a recent Australian study looking at 3212 patients undergoing angiography for AMI, only 48% of patients were referred to CR [12], with numbers in the UK, USA and Europe ranging between 30 and 50% [13]. Additionally, attendance attrition rates in CR programs may reach up to 60% over the course of the program and represents a significant ongoing challenge [14]. Globally there have been cost challenges associated with CR attendance. Suaya JA et al. in the US reported that just over 13% of Medicare patients who had suffered an AMI, and 30% after CABG, received CR services after index hospitalisation [15]. Moreover, there may be a particular subset of the population including women, elderly people, those with significant comorbidities and those with inadequate health insurance coverage that are less likely to participate in or receive CR despite its proven protective effect [15, 16].

CR programs play a vital role in the development of personalized weight optimization strategies and education regarding risks of inactivity and reinforcing the positive benefits of regular physical exercise. Despite guideline recommendations of at least 150 min of moderate-intensity aerobic physical activity or 75 min of vigorous-intensity activity throughout the week, evidence suggests that the majority of individuals do not meet this target [17]. The recent 2014/15 Australian Health survey found that over 70% of the adult population had sedentary or low levels of physical activity, not meeting guideline recommendations [18]. There has been efforts to quantify activity levels. Previously published literature has used pedometer-determined physical activity to identify under-activity and suggest daily targets, with an average step count of less than 5000 steps per day defined as sedentary, 5000–7499 as low activity, 7500–9999 as ‘somewhat active’ and greater than 10,000 steps per day as ‘active’. Individuals who take greater than 12,500 steps per day are classified as ‘highly active’ [19]. Numerous studies have shown the significant benefit of regular physical activity with an up to 30–40% reduction in CV risk when compared to inactive individuals [20, 21].

The new generation of wearable consumer personal activity trackers, incorporating a pedometer and accelerometer, offer unique opportunities to engage and remotely monitor patients engaged in rehabilitation programs with exercise components. These devices, offering sophisticated features such as GPS tracking, heart rate monitoring, activity and sleep tracking with smart phone application integration, give individuals an easy and affordable way to monitor physical activity and energy expenditure with the majority of devices showing acceptable validity of the data recorded [22, 23]. It is estimated that approximately 25 million of these devices were sold in 2015 with worldwide sales expected to increase to 12.6 billion US dollars by 2018 [24]. Wrist-worn monitors are predicted to account for 87% of the devices sold [25].

The use of older generation pedometers is well documented in the medical literature. A systematic review and meta-analysis of 8 randomized controlled trials and 18 observational studies with a total of 2767 patients found an increase in physical activity of 26.9% over baseline as measured by step count in patients using pedometers, with significant reduction in body mass index and blood pressure [26]. An important predictor of increased physical activity was having a daily step goal of 10,000. More recently, a systematic review of 11 studies including 1272 participants across 5 countries concluded that wearing electronic activity monitoring systems lead to an increase in physical activity and decrease in weight, suggesting potentially clinically significant benefits [27]. Indeed, a significant advantage of a mobile device-based study is that participants naturally take the device with them, permitting passive recording of motion however, but its feasibility and validity on a 6-min walk test was questioned in a recent study by McConnell et al. [28]. A combination approach with measures of physical activity through a personal activity tracker and formal serial physical assessments of 6-min walking test perhaps is a more accurate assessment.

One of the limitations to these devices is the documented low rates of long-term engagement for many users [15, 29, 30]. Some have suggested that compliance at two years is approximately 40% [31]. However, despite these concerns, long-term compliance has not been assessed in patients post acute coronary syndrome. It could be argued that given the often life threatening event spurring behaviour change, engagement and compliance may well be higher.

## Aim

The aim of this study is to assess the impact of personal activity trackers on exercise capacity, and improvement of cardiovascular risk factors including blood lipids, blood glucose, mood, weight, waist circumference, body mass index, blood pressure, exercise motivation and quality of life (QOL) in post acute coronary syndrome patients undergoing cardiac rehabilitation,

## Hypotheses

The primary hypothesis is that the use of a personal activity tracker will improve exercise capacity, as measured by an objective 6-min walk test, compared to standard care alone. The secondary hypotheses are that the use of personal activity trackers will result in the improvement in cardiovascular risk factors, namely; improved lipid profile, blood pressure, BMI, weight and waist circumference, HbA1c (where applicable) as well as an improvement in psychological status, mood, exercise motivation and QOL.

## Methods/Design

UP-STEP ACS is a prospective single-blinded, two-arm, parallel, randomized control trial with an aim to enrol 200 patients (100 in each arm). The study design is displayed in Fig. 1. This protocol is prepared based on the SPIRIT 2013 statement [32].

**Fig. 1 Fig1:**
[figure not shown]
Randomized control trial design and flow

### Outcome assessment

#### Primary outcome

The primary outcome is a change in six-minute walk distance that will be measured in a standardized fashion as per the American Thoracic Society Statement 2002 [33]. The initial test will be undertaken during index hospital admission with telemetry monitoring and will be repeated at eight weeks as an outpatient. It will be undertaken by a trained assessor.

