#### Secondary outcomes

All secondary outcomes will be measured at baseline and at 8-week follow-up. Table 1 summarizes the secondary outcomes of our study. In addition to those already mentioned, a number of self-reported indices will be recorded at follow-up appointment. Namely, smoking status, date participants returned to work (if applicable), medication adherence, and cardiac rehabilitation attendance and completion, defined as attending all sessions. Any major adverse cardiovascular events (MACE) will be recorded. MACE is defined as the composite of death, non-fatal myocardial infarction, stroke and unplanned revascularization. In addition, cardiac related hospital admissions will also be documented. Both primary and secondary outcomes are outlined in Table 1.

**Table 1 Tab1:** Primary and Secondary endpoints

Primary Outcome
• Six-minute walk test distance
Secondary Outcome
• Fasting Lipid Levels
• Fasting Glucose
• Resting Blood Pressure
• Resting Heart Rate
• Weight and Body Mass Index (BMI)
• Waist Circumference
• Smoking Status (self-Reported)
• Attendance and adherence to Cardiac Rehabilitation
• Depression/Mood Assessment
• Compliance with Secondary Prevention Pharmacotherapy
• Exercise Motivation (EMI-2)
• Quality of Life

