### Sample size required

We calculated that 152 participants (76 in both the intervention and control groups) would need to be enrolled for the study to have a statistical power of 80% to detect a clinically important increase of 25 m in the six-minute walk test [21, 22], in the intervention group as compared with the control group, with a two-sided alpha level of 0.05. Accounting for 20% loss to follow-up a minimum of 92 patients in each arm will be required. If the power was to increase to 90% at 5% level of significance 101 patients would be required in each arm of the study. We plan to recruit 100 patients in each arm, totalling 200 patients.

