### Randomization

Once all screening assessments are completed and eligibility is confirmed patients (*n* = 200) will be randomized in a 1:1 fashion to receiving the personal activity monitor (Fitbit Charge 2) in addition to usual cardiac rehabilitation or the usual cardiac rehabilitation alone through a computer based randomization process (Fig. 1). A computer-generated table will allocate patients in fixed blocks of four. In order to prevent selection bias, the allocation sequence will be concealed from the investigators enrolling and assessing patients utilizing computer randomization software.

Baseline patient demographics and pre-defined screening and assessment, including the 6-min walk test, will occur prior to randomization after patients have given informed consent. Assessors of the primary outcomes will be blinded to the treatment allocation, however participants are not able to be blinded.

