### Statistical analysis

The intervention arm will be compared against the control arm on an intention to treat analysis basis. All statistical analyses will be performed using SPSS v23 (IBM, USA). Baseline characteristics will be summarized using descriptive statistics. Paired Student-t test will be used for all normally distributed continuous variables and will be described as mean with standard deviation. Variables not normally distributed will be analysed using the Wilcoxon Signed Rank test. Categorical variables will be described as frequencies and percentages and will be compared using a Pearson chi-squared test.

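### The stated analysis of change in six-minute walk distance does not adjust for the pre-randomisation walk, so an unadjusted between-arm comparison would forgo precision that costs nothing to keep

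*Protocol article*

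**What the plan says.** All of this is in the protocol article.

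- **Primary outcome:** "The primary outcome is a change in six-minute walk distance that will be measured in a standardized fashion". On timing: "The initial test will be undertaken during index hospital admission with telemetry monitoring and will be repeated at eight weeks as an outpatient".
- **Table 1 (under Secondary outcomes):** the primary endpoint is listed as "Six-minute walk test distance", without the word change.
- **Randomization:** baseline assessments, "including the 6-min walk test, will occur prior to randomization after patients have given informed consent". Allocation is 1:1.
- **Statistical analysis:** the arms are to be compared by intention to treat. Normally distributed continuous variables get a paired t test. For the rest, "Variables not normally distributed will be analysed using the Wilcoxon Signed Rank test". No regression model, covariate or between-arm estimate in metres is named.
- **Sample size required:** 76 per arm for 80% power to detect 25 m, "with a two-sided alpha level of 0.05"; 101 per arm for 90% power; 20% loss to follow-up allowed for; 100 per arm planned. Neither an SD nor a correlation is given.

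**The concern.** The paired and signed rank tests compare visits within an arm and do not estimate the difference between arms. That is a separate and more serious defect. The obvious repair, an unpaired t test on change, would still leave the present point open.

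Subtracting baseline forces its coefficient to be 1, whereas a model with baseline as covariate estimates that coefficient. The first walk is done on the ward under telemetry and the second as an outpatient eight weeks later, so there is no particular reason to expect a coefficient of 1. With equal SDs at the two visits, change is noisier than week-8 distance alone whenever the correlation is below 0.5. At stake is the precision of the primary comparison, from data the trial collects anyway.

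The route for non-normal data adds to this. A signed rank test gives no between-arm mean difference to set against the 25 m target.

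**Working it through.** **Inputs from Sample size required.** Difference 25 m, two-sided alpha 0.05, 76 per arm at 80% power, 101 per arm at 90% power, 100 per arm planned, 20% loss. Evaluable: 100 × 0.8 = 80 per arm.

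**Not in the document, so assumed.** What kind of SD lies behind the calculation, the ratio of the SDs at the two visits, and the correlation ρ between baseline and week 8 (range shown: 0.3 to 0.9).

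**Step 1: the plan's own figures.** Without an SD, 76 cannot be reproduced directly. Solving n = 2·SD²·(z₀.₉₇₅ + z_power)²/25² for SD gives:
- 76 per arm, 80%: SD = 25·√(76/2)/(1.960 + 0.842) = 55.0 m
- 101 per arm, 90%: SD = 25·√(101/2)/(1.960 + 1.282) = 54.8 m

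The two stated sizes agree with each other at an SD of about 55 m. With 80 evaluable per arm and SD 55 m, the standard error is 55·√(2/80) = 8.70 m. Power is 82.0% by the normal approximation and 81.5% by the t test.

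**Step 2: 55 m is the SD of change, with equal SDs at both visits.** The residual variance after adjustment is (1+ρ)/2 times the variance of change, so the adjusted SD is 55·√((1+ρ)/2).

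| ρ | Adjusted SD (m) | Power, normal | Power, t | Gain (normal) |
|---|---|---|---|---|
| 0.3 | 44.3 | 94.6% | 94.3% | 12.6 |
| 0.5 | 47.6 | 91.3% | 91.0% | 9.3 |
| 0.7 | 50.7 | 87.7% | 87.3% | 5.7 |
| 0.8 | 52.2 | 85.8% | 85.4% | 3.8 |
| 0.9 | 53.6 | 83.9% | 83.4% | 1.9 |

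**Step 3: 55 m is the SD of a single distance, with equal SDs.** The SD of change is 55·√(2(1−ρ)); the adjusted SD is 55·√(1−ρ²).

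| ρ | SD of change (m) | Power, change | Adjusted SD (m) | Power, adjusted | Gain |
|---|---|---|---|---|---|
| 0.3 | 65.1 | 68.1% | 52.5 | 85.4% | 17.3 |
| 0.5 | 55.0 | 82.0% | 47.6 | 91.3% | 9.3 |
| 0.7 | 42.6 | 96.0% | 39.3 | 98.1% | 2.1 |
| 0.8 | 34.8 | 99.5% | 33.0 | 99.8% | 0.3 |

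These are normal-approximation values. The t test at ρ = 0.3 gives 67.5% and 85.0%. At ρ = 0.5 the two readings of 55 m coincide.

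**Step 4: unequal SDs, 55 m as the SD of change.** With k = follow-up SD / baseline SD, the variance ratio is k²(1−ρ²)/(1+k²−2ρk). Over ρ from 0.5 to 0.9, the gain is 0.1 to 5 points for k = 1.2 and 13 to 15 points for k = 0.8.

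The gain is never negative. Apart from one degree of freedom, with 1:1 allocation the adjusted analysis is no less precise than raw change at any correlation. Equal SDs are needed only for the (1+ρ)/2 formula and for the 0.5 threshold.

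**The case against.** **The document does not fix an unadjusted analysis.** A reader might infer from the outcome definition that raw change is laid down. It is not: a change endpoint can carry baseline as a covariate, and an analysis plan that is not shown may do that. This stands as a limit on the wording. It does not remove the point, because the Statistical analysis section is not silent. It assigns named tests to every continuous variable, and none of them uses baseline as a covariate.

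**The power loss is not a property of the trial.** A reader might take a figure such as 4 to 13 points as what the trial gives up. That span needs 55 m to be the SD of change, equal SDs and ρ between 0.8 and 0.3, none of which the document states. Across the scenarios above the gain runs from about 0 to about 17 points. This objection stands in full.

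**Nothing falls short or is biased.** If 55 m is the SD of change, unadjusted power with 80 per arm is about 82%, above the planned 80%. Under randomisation a comparison of change is valid. A chance baseline imbalance moves the estimate, but that is sampling error already in its standard error. This too stands. The one case below 80% (about 68%) needs 55 m to be the SD of a single distance and ρ near 0.3; the document neither supports nor excludes it.

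**Table 1 is only a list of labels.** A reader might see two competing primary endpoints. The other entries also omit change although they are measured at both visits, and the Abstract and Discussion speak of change or improvement. This is loose labelling, not a contradiction.

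**Rank methods can give an estimate in metres.** A Hodges–Lehmann estimate can accompany them. That is true, but the plan names none, and the signed rank test it names is within-arm.

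**Conclusion.** The point holds as an avoidable loss of efficiency. The outcome is change, a valid baseline covariate is collected before randomisation, and the stated analysis does not use it. An unadjusted comparison of change would remain less precise even after the paired tests are corrected.

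The size depends on assumptions. At a correlation of 0.5 with equal SDs, both readings of 55 m give about 82% rising to 91%. Elsewhere the gain may be close to nothing or as much as 17 points. The direction is secure; the amount is not. The documents do not support calling this bias or an underpowered trial. It should be changed because the improvement is free.

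**What to change.** In the Statistical analysis section, name one primary analysis: a linear model of week-8 six-minute walk distance on randomised arm, with baseline distance as covariate. Report the adjusted between-arm difference in metres with a 95% CI, read against 25 m. Keep this model as primary whatever the distribution looks like, with any rank-based analysis as sensitivity.

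Use the same model for continuous secondary outcomes that have a baseline value: blood pressure, heart rate, weight, BMI, waist, lipids, glucose and questionnaire scores.

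With baseline in the model, the treatment estimate is the same whether the outcome is called change or week-8 distance. The Primary outcome text and Table 1 can therefore share one wording. It would also help to state in Sample size required the SD used and whether it refers to change or to a single distance.

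The cost is wording only: no extra patients, visits or data, and the model is standard in the named software.

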#### Secondary outcomes

All secondary outcomes will be measured at baseline and at 8-week follow-up. Table 1 summarizes the secondary outcomes of our study. In addition to those already mentioned, a number of self-reported indices will be recorded at follow-up appointment. Namely, smoking status, date participants returned to work (if applicable), medication adherence, and cardiac rehabilitation attendance and completion, defined as attending all sessions. Any major adverse cardiovascular events (MACE) will be recorded. MACE is defined as the composite of death, non-fatal myocardial infarction, stroke and unplanned revascularization. In addition, cardiac related hospital admissions will also be documented. Both primary and secondary outcomes are outlined in Table 1.

**Table 1 Tab1:** Primary and Secondary endpoints

Primary Outcome
• Six-minute walk test distance
Secondary Outcome
• Fasting Lipid Levels
• Fasting Glucose
• Resting Blood Pressure
• Resting Heart Rate
• Weight and Body Mass Index (BMI)
• Waist Circumference
• Smoking Status (self-Reported)
• Attendance and adherence to Cardiac Rehabilitation
• Depression/Mood Assessment
• Compliance with Secondary Prevention Pharmacotherapy
• Exercise Motivation (EMI-2)
• Quality of Life

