### Exercise prescription

Patients in both groups will be encouraged to exercise as per guideline recommendations [17] over the course of the study period. Patients in the intervention arm will be encouraged to meet a target of at least 10,000 steps per day, with the device programmed to this goal. In men who underwent an exercise rehabilitation program, improvement in walking distance (i.e. steps per day) was a strong independent predictor of survival, and a useful guide to prognosis [36] The study coordinators will be able to view these de-identified step counts in real time, however there will be no further interaction with patients in either group until the 8-week follow-up review.

The routine community cardiac rehabilitation program that all will be encouraged to attend encourages patients to engage in regular moderate intensity exercise increasing in a graded degree over a seven-week period centred around a walking program. Moderate intensity is described as exercise that is ‘neither too hard, nor too easy’, with ‘mild shortness of breath, sweating and increased heart rate’ as per the National Australian Heart Foundation recommendations [37].

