### Cardiovascular health education

All patients will undergo regular cardiac rehabilitation sessions as run by the health service. This incorporates an extensive teaching program around cardiovascular health education, risk factor modification, exercise prescription and dietary advice along with the implications of psychological stress on cardiovascular disease. This program is run in a group setting with family members invited to attend. It is available at various times throughout the week to facilitate high attendance rates. It is run over either a 6-week period incorporating weekly daytime sessions or over 4 weeks incorporating longer evening sessions to facilitate patients with work commitments.

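### Cardiac rehabilitation attendance, a secondary endpoint, rests on self-report by unblinded patients and an all-or-nothing completion rule; session records would remove a risk of bias at little cost

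*Protocol article*

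**What the plan says.** Under Secondary outcomes, the article states that "a number of self-reported indices will be recorded at follow-up appointment" and includes in that list "cardiac rehabilitation attendance and completion, defined as attending all sessions". Table 1 in the same section names the endpoint differently, as "Attendance and adherence to Cardiac Rehabilitation".

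Under Randomization: "Assessors of the primary outcomes will be blinded to the treatment allocation, however participants are not able to be blinded". Assessor blinding is thus stated for the primary outcomes only. Under Eligibility and recruitment, agreeing to complete rehabilitation is an inclusion criterion for every patient.

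Under Cardiovascular health education: "All patients will undergo regular cardiac rehabilitation sessions as run by the health service". On format, the same section says: "It is run over either a 6-week period incorporating weekly daytime sessions or over 4 weeks incorporating longer evening sessions". Under Exercise prescription, the routine community programme is said to encourage moderate exercise "increasing in a graded degree over a seven-week period centred around a walking program".

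Under Statistical analysis: "Categorical variables will be described as frequencies and percentages and will be compared using a Pearson chi-squared test". The study period is 8 weeks from discharge (Primary outcome and intervention).

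**The concern.** Two features weaken this endpoint.

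The first is the source. Patients who know their arm, and who promised at entry to complete the programme, are asked at week 8 whether they did. The body that runs the sessions could be expected to know who attended, but the article does not name it as the source. If patients given a tracker over-report more, or less, than controls, the difference between arms is partly a difference in reporting.

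The second is the definition. Completion is yes or no, and the same rule covers two formats of different length. It is also read at a fixed 8 weeks after discharge, whenever the patient started. Someone who began late and has missed nothing may still be mid-course and count as a non-completer.

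At stake is whether a reported effect of the tracker on rehabilitation adherence, which the abstract names as a secondary endpoint, can be believed and interpreted.

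**Working it through.** The article gives no completion rate, session count or power for this endpoint, so there is no figure to reproduce. The check is first textual, then illustrative. All rates below are assumptions.

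**1. Is the endpoint self-reported?** Yes. In Table 1 only smoking status carries a self-report label, but the text above the table puts rehabilitation attendance and completion in the self-reported list. No attendance record is mentioned.

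**2. What could arm-dependent over-reporting do?** Let true completion be π in both arms, and let a fraction m of tracker-arm non-completers report completion while controls report truthfully. The spurious difference is (1 − π) × m. The chance of a significant result favouring the tracker uses the normal approximation for two proportions (two-sided 5%, 100 per arm, no loss to follow-up); its nominal value in one direction is 2.5%.

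| π | m = 5% | m = 10% | m = 20% |
|---|---|---|---|
| 40% | 3.0 points; 6.3% | 6.0 points; 13.5% | 12.0 points; 39.8% |
| 50% | 2.5 points; 5.4% | 5.0 points; 10.5% | 10.0 points; 29.4% |
| 60% | 2.0 points; 4.7% | 4.0 points; 8.4% | 8.0 points; 21.6% |

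For example, with π = 40% and m = 10%: 0.60 × 0.10 = 0.06. The range for π is assumed; for context, the Background cites attrition of up to 60% in such programmes. If m is the same in both arms, the difference under the null is zero.

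**3. What does the all-sessions rule do across formats?** Assume each session is attended independently with probability p. The 6-week format is weekly, hence 6 sessions. No count is given for the 4-week format; 4 is assumed. Completion probability is p⁴ or p⁶. The effect on the arm comparison is d × (p⁴ − p⁶), where d is the difference between arms in the share of patients using the 4-week format.

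| p | 4 sessions | 6 sessions | Gap between formats (points) | Between arms, d = 10 points | Between arms, d = 20 points |
|---|---|---|---|---|---|
| 0.80 | 41.0% | 26.2% | 14.7 | 1.5 | 2.9 |
| 0.90 | 65.6% | 53.1% | 12.5 | 1.2 | 2.5 |
| 0.95 | 81.5% | 73.5% | 7.9 | 0.8 | 1.6 |

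(Gaps are taken before rounding.) Identical behaviour gives quite different completion rates by format, but with d = 0 there is no difference between arms, and with d = 10 points it is only 0.8 to 1.5 points.

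**4. Can every patient finish by week 8?** The article fixes no start date for rehabilitation. Six full weeks fit only if the course starts by week 8 − 6 = 2 after discharge. Counting from first to last weekly session (5 weeks), the limit is week 8 − 5 = 3. Later starters cannot be completers at the visit. This cut-off is the same in both arms.

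**5. Are the terms and durations consistent?** Table 1 speaks of adherence and the text of completion; only completion is defined. The seven weeks under Exercise prescription describe a graded walking period attributed to the routine programme, whose sessions are elsewhere said to run for 6 or 4 weeks. The article does not say how the two relate.

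**The case against.** The strongest reply is that nothing here is shown to separate the arms. Every patient, tracker or control, agreed to complete rehabilitation, so both have that reason to over-report. The device is handed over before discharge, and nothing makes keeping it depend on later attendance. Equal misreporting produces no spurious difference under the null. This stands, and it limits the point to a risk. It does not remove the risk: patients are unblinded, only one arm received something in connection with the agreement (Primary outcome and intervention), and no safeguard is stated for this endpoint.

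A reader might infer that mixing formats makes the arms incomparable. The documents do not support that. Randomisation balances format in expectation, and the large gaps in step 3 are between formats, not between arms.

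A reader might also infer three session schedules of 4, 6 and 7 weeks. The seven weeks describe exercise progression and are not clearly a session schedule, so a calculation on 7 sessions would have no firm basis. Only clarification is needed.

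Finally, attendance is recorded alongside completion, so the all-or-nothing rule is not the sole measure. That is correct and softens the loss of information, but attendance is self-reported too and the article gives it no definition.

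**Conclusion.** The point holds as a risk of bias in one secondary endpoint, together with a definition that is hard to interpret. It does not establish that the endpoint is biased. If over-reporting were confined to the tracker arm, at 10% of its non-completers, the spurious difference would be 4 to 6 points and the one-directional false-positive rate 8% to 14%; at 20% they would be 8 to 12 points and 22% to 40%. These figures rest on the assumed completion range of 40% to 60%, truthful reporting by controls and 100 evaluable patients per arm. With equal misreporting the distortion under the null is nil. The format and late-start problems cost information and interpretability; they reach the arm comparison only if format mix or start time differs by arm. The six-minute walk endpoint and the sample size are untouched. This is a minor recommendation, worth making because a better source should be within reach.

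**What to change.** - Take attendance from the health service's session records, read after each patient's scheduled programme end, and use self-report only where no record can be obtained.
- Make the measure sessions attended divided by sessions scheduled for the patient's format, with completion per format as a supplementary measure.
- Do not adjust the arm comparison for format. Rehabilitation follows discharge and randomisation precedes it, so format may be chosen after allocation and be influenced by it; the format-specific denominator already deals with length.
- Use one term, defined once, in Table 1 and the text.
- Clarify how the seven-week walking period under Exercise prescription relates to the 6- and 4-week programmes under Cardiovascular health education.

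The cost is retrieval of attendance records for 200 patients, some of them after the 8-week visit, and the rewording of one definition. That such records exist and can be obtained is an inference from the health service running the sessions, and should be confirmed first.
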